### Study Population

Principal inclusion criteria were age 21-80 and the presence of at least one coronal or root surface cavitated caries lesion (either present at screening or documented in the dental record within the past 12 months). The caries criterion was designed to include participants who were at risk of forming new lesions. Similarly, to ensure an adequate quantity of surfaces at risk, participants were required to have a minimum of 12 teeth with exposed coronal or root surfaces. In addition, participants had to be able to read and comprehend study materials in English, and be able to give informed consent. Exclusion criteria consisted of having more than 10 teeth with caries lesions, having Type IV periodontitis, receiving long-term antibiotic therapy, needing antibiotic prophylaxis prior to dental treatment, having history of head and neck radiation therapy, a history of adverse reaction to either placebo or intervention agent, a serious illness that would interfere with participation, plans to leave the area within the next three years, no telephone, a member of the household already enrolled in the trial, or investigator option.

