### Recruitment, Run-in and Enrollment

Recruitment of potential study participants began in April 2007, and ended in September 2008. Although the primary pool of potential study participants was dental school patients, low yields prompted two sites to expand recruitment efforts to the general public via solicitations at public dental clinics and mass media advertising. All enrollment visits were preceded by a brief conversation by telephone or in person during which eligibility and interest were assessed. Where possible, additional initial screening was accomplished by review of electronic or paper clinical records. All potential study participants attended an enrollment visit where eligibility was verified, the study was described, and requirements of participation were reviewed. Those individuals who indicated a willingness to enroll participated in a four-week run-in period [10] to help identify potential participants who were unable or unwilling to adhere to the study regimen. A call midway through the run-in period was used for data collection (adherence, side effects) and encouragement. Ultimately, 27% of those who entered the run-in period did not continue to randomization [11]. Enrollees received no financial incentives for participation in the run-in period. Financial incentives, in the form of cash payments and travel expense reimbursements, were available for enrollees who continued to the full trial.

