### Randomization and Treatment Contacts

Those enrollees who completed the run-in period with adequate self-reported adherence (consumption of more than half of lozenges scheduled during the run-in period) and who indicated a willingness to participate in the full trial attended a baseline visit wherein eligibility criteria were confirmed, and a caries examination was performed. Eligible enrollees were randomized to either the active or placebo arm, additional information was collected, and the initial supply of lozenges was dispensed. Randomization was carried out using a web-based randomization application process. Allocation assignments were stratified by site and age group (≥ 50, < 50 yrs.) in permuted blocks of varying sizes within each stratum. Staff and participants were blinded to treatment assignment. A total of 691 participants were randomized, 92% of the goal of 750.

In the periods between the visits for caries examinations, participants are contacted by telephone on a quarterly basis to assess adherence, side effects, receipt of preventive dental care; to screen for possible serious adverse events; and to arrange for re-supply of lozenges. Participants are asked how many unopened bottles they have on hand, and sufficient bottles for the next three months are dispensed from the participant's master supply at the clinical site and are delivered by courier.

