### Sample Size

We based our required sample size on a series of large longitudinal cohort studies that permitted estimates of expected combined net D_2_FS increment in the placebo group of the trial. These studies, reviewed by Griffin et al. [16] and Thomson [1] did not include measurement of D_1 _lesions. Although they varied in design, these studies reported sufficient data to calculate reasonable values for three-year untreated incidence rates of root, coronal, and total caries, under the assumption of constant rates over years. These estimated surface increments were 1.4, 2.5 and 3.7 respectively. We estimated the sample size needed, using a range of values (2.3 to 4.9) for the placebo cumulative, combined D_2_FS increment over three years, and assuming that the treatment might result in a 20% reduction, with power set at 80% and one-sided alpha at 0.025. Using PASS 2005 with a Poisson regression model and a large, but plausible overdispersion parameter (3.0, to account for excess variability), and assuming attrition of 10% per year, we obtained a sample size target of 250 at each clinical site (750 total).

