#### Primary Outcome Analysis

The primary analyses will be an intent-to-treat (ITT) analysis, on a sample that includes all randomized patients and classifies them according to their assigned treatment group, regardless of their adherence to the protocol. The primary outcome will be analyzed in a negative binomial regression model (using SAS^® ^PROC GENMOD) in which treatment group and clinical center indicators are included as fixed categorical design factors. Planned (*a priori*) covariates are age and age-squared, intensity of preventive regimen, oral hygiene behavior measures, and severity of baseline caries, which is defined as the sum of decayed surfaces at the baseline examination. We will include the natural log of person-years at risk, ln(*t *_i_), as an offset to adjust for length of time since the participant was randomized. Formally, the model is,

ln(μi)=β0 +  Tiβ1+ S1β2 + S2β3 + ci'γ + ln(ti),

or equivalently,

ln(μi/ti) = β0 + Tiβ1 + S1β2 + S2β3++ ci'γ,

where *μ *is the mean observed increment, *μ */t is the incidence of new progressions per year, T is the treatment indicator (0 = placebo, 1 = xylitol), S_1_, S_2 _are clinical site indicators, **c**_i _represents a vector of covariates, and **β **and **γ **represent vectors of parameters to be estimated. The resulting *β*_1 _coefficient thus has the interpretation of the ln(relative risk) for progression for the xylitol compared to placebo lozenges, and the null hypothesis test of no difference between treatment arms is a test of H_0_: *β*_1 _= 0 vs. the alternative hypothesis H_1_: *β*_1 _< 0. The actual fraction of a year's exposure to the lozenges will be used where known, otherwise, the offset will be set to the midpoint of the period between the first examination missed and the last examination attended. In secondary analyses of the primary outcome, we will conduct sensitivity analyses by applying the alternative distributional models (Poisson, mixture models) mentioned above to the same data.

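### The baseline-severity covariate counts only surfaces decayed at the baseline examination, so a participant admitted on a recorded lesion can score zero and some precision is given up

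*Protocol article*

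**What the plan says.** Under Study Population, the protocol article requires at least one cavitated lesion, "either present at screening or documented in the dental record within the past 12 months". It gives the reason: "The caries criterion was designed to include participants who were at risk of forming new lesions". An upper limit excludes anyone "having more than 10 teeth with caries lesions".

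Under Recruitment, Run-in and Enrollment, "the primary pool of potential study participants was dental school patients", and those willing to enroll "participated in a four-week run-in period". The baseline caries examination comes after that run-in (Randomization and Treatment Contacts). On allocation, "Allocation assignments were stratified by site and age group", so caries severity is not a stratification factor.

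Under Primary Outcome Analysis, the negative binomial model has treatment, clinical center, age and age-squared, intensity of preventive regimen, oral hygiene behavior, and "severity of baseline caries, which is defined as the sum of decayed surfaces at the baseline examination". It has no term for filled surfaces or for how the participant qualified. The section does not say which examination codes count as decayed.

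**The concern.** The entry rule recognizes caries activity in two ways, an open lesion or a recent record of one. The severity covariate recognizes only the first. Two participants with the same recent caries experience can therefore score differently because one had the lesions treated before the baseline examination. To that extent the covariate mixes caries activity with receipt of care.

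A covariate that measures activity imperfectly explains less of the variation between participants, and the standard error of the treatment effect is then larger than the collected data require. Precision matters here. Enrollment reached 691 of 750 and the final examination moved from 36 to 33 months, so person-time before attrition is about (691/750) × (33/36) = 0.921 × 0.917 = 0.84 of what was planned. Because severity is not stratified, adjustment for it rests on this covariate.

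**Working it through.** **1. The definitions side by side.** An open lesion at screening already satisfies the first entry route, so the record route matters only for people without one seen at screening. Their recorded lesion may have been restored. If so, and if they have no other decayed surface, the covariate is zero. Filled status is scored surface by surface at the same examination (Caries Examination), so the information is already held. In Table 1 the D2 row has no positive weight, whereas F to FD2 scores +1. A surface counted by the covariate cannot add to the outcome in its next transition, while an uncounted filled surface can.

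**2. The plan's own sample size.** Inputs from Sample Size: placebo increment μ = 3.7, rate ratio 0.80, overdispersion φ = 3, "with power set at 80% and one-sided alpha at 0.025", attrition 10% per year. Poisson regression with a 1:1 treatment indicator:

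N = φ (z₀.₉₇₅√4 + z₀.₈₀√(2 + 2/0.8))² / (μ (ln 0.8)²) = 3 × (3.920 + 1.785)² / (3.7 × 0.0498) ≈ 531 evaluable.

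Dividing by retention gives 728 (0.729, compounded) or 758 (0.70, linear), both within 3% of 750. No covariate enters the formula, so the choice of covariate does not alter the target.

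**3. Bias and direction (assumed values).** Simulation with 504 completers (691 × 0.729), mean 3.7, variance/mean 3 and rate ratio 0.8. One latent activity drives a mean of 3 lesions in 12 months as well as the outcome, and restored participants score exactly zero. Quasi-Poisson model, 400 runs per row. Power = Φ(0.2231/SE − 1.960); for example 0.2231/0.0726 − 1.960 = 1.113, so power is 0.867.

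| Covariate | Share restored | SE | Power |
|---|---|---|---|
| none | – | 0.0822 | 0.775 |
| total 12-month experience | – | 0.0646 | 0.933 |
| decayed only | 10% | 0.0726 | 0.867 |
| decayed only | 25% | 0.0770 | 0.825 |
| decayed only | 50% | 0.0802 | 0.795 |
| decayed only | 75% | 0.0814 | 0.783 |

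Adding an indicator of restored entry to the decayed count gave SEs of 0.0662, 0.0693, 0.0740 and 0.0783 for the four shares. Mean estimates lay between −0.217 and −0.230, against ln 0.8 = −0.223, so no bias appears. The 0.0646 is a ceiling: an undated filled count does not measure 12-month experience.

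**4. Gain from adding the filled count (assumed values).** n = 691, placebo mean 3.4 (3.7 × 33/36 = 3.39), rate ratio 0.8. Variance reduction = 1 − (SE with filled / SE without)².

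- *Fillings from recent lesions only* (propensity SD 0.5 or 0.8; 25–50% of past lesions untreated; 60 trials per scenario). SD 0.5: 0.0715 to 0.0677, 10%, and 0.0709 to 0.0679, 8%. SD 0.8: 0.0840 to 0.0722, 26%, and 0.0798 to 0.0720, 19%.
- *Lifetime fillings* (0.7 per year from age 10; access-to-care SD 0.6; correlation of lifetime with current propensity 0.3–0.7; 60 trials per scenario). Reduction 1–8%; for example 0.0562 to 0.0556 is 2%, and the largest, 0.0728 to 0.0698, is 8%.
- *Lifetime fillings plus a route indicator* (propensity SD 0.7; on average 10 or 25 age-driven filled surfaces, loosely tied to propensity). Reduction 9–10%, 14% and 16–18% when 10%, 25% and 50% entered on restored lesions. The indicator alone gave about 5–9%.

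**The case against.** An eligibility rule and a prognostic covariate need not share a definition. The covariate is prespecified and measured before treatment, and it gives a valid analysis. That stands, and it limits the point to efficiency.

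A reader might infer that record-route participants were already treated and score near zero. The article says neither. Initial screening included a telephone or in-person conversation and, where possible, chart review, so a recorded lesion could still be open at baseline. Such participants may have other decayed surfaces, and if non-cavitated D1 lesions count, zero scores become less common. The share entering by record only is not given. What stands is that a zero score is possible.

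Table 1 also cuts both ways. The F row has one positive cell and the sound row has three, so filled surfaces are themselves largely out of risk. This removes any surface-level argument that filled counts must predict strongly. Their value would lie in marking the person's caries experience, and the model estimates that coefficient freely.

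Site indicators, preventive regimen and oral hygiene may absorb part of the care-seeking difference. They do so only in part: site terms remove average differences between centers, not differences within a center.

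Finally, fillings in adults aged 21–80 are undated and accrue over decades. This is the strongest objection to any large figure, and the lifetime-fillings simulation bears it out: the gain from the filled count alone fell to 1–8%.

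**Conclusion.** The mismatch between the entry rule and the covariate is in the text. Its consequence is a modest loss of precision relative to a covariate set that the baseline examination already supports. The size cannot be derived, because the documents do not give the share entering by record only, the baseline distribution of decayed surfaces or the prognostic value of either count. On assumed values, a variance reduction of roughly 1–10% is a fair illustration once lifetime fillings are allowed for, which is about 0.5–5% of the standard error (1 − √0.99 to 1 − √0.90). The 19–26% figures need high variation in propensity and fillings that are mainly recent. The 14–18% figures need a route indicator and at least a quarter of participants entering on restored lesions.

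A reader might also infer that the primary comparison is biased, that type I error is inflated or that 750 was too small for this reason. The documents support none of these: the covariate is fixed before randomization, the simulated estimates stay near ln 0.8, and the sample size claims no gain from adjustment.

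**What to change.** In Primary Outcome Analysis, before unblinding:

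1. State which codes count as decayed: D2 and D3, with or without D1, and whether decay on filled or crowned surfaces (such as FD2) is included. Keep this term.
2. Add the number of filled surfaces at the baseline examination as a separate covariate.
3. Add an indicator of entry route (lesion present at screening versus record only) only if the route was recorded when eligibility was verified. Define it for participants who qualify both ways. The article does not show that the route exists as an analyzable variable.

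Steps 1 and 2 cost a sentence or two and one model term and need no new data. Because the count is fixed before randomization, prespecifying it cannot bias the comparison.

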### Caries Examination

Caries are diagnosed visually by calibrated examiners using a CPITN-E probe, a non-magnifying plane mirror; and standard dental operating light and chair. Loupes are used at the discretion of the examiner, but consistently within each examiner. Tooth surfaces are dried for five seconds with an air/water syringe.

The X-ACT examiners use the nomenclature of Pitts and Fyffe [12] to classify the status of each tooth surface; however, the descriptors in X-ACT are a modification of the 2-digit numeric codes in the International Caries Detection and Assessment System II (ICDAS II) [13,14]. ICDAS II has established objective clinical signs that are associated with severity levels of dental caries, verified histologically. The X-ACT taxonomy does not make a number of distinctions that are in the ICDAS II taxonomy. Instead, we have collapsed codes as follows:

• First digit codes: 0 is signified by S(sound); 1, 2 are collapsed into P (pits and fissures sealed surface); 3, 4, 7, 8 are collapsed into F(filled); and 5, 6 are collapsed into C(crowned);

• Second digit codes: 0 is signified by S; 1, 2 are collapsed into a single D_1 _code (uncavitated lesion); 3, 4 are collapsed into a single D_2 _code (cavitated lesion penetrating the enamel); and 5, 6 were collapsed into a single D_3 _code (cavitated lesion penetrating into the dentin).

• Codes 97, 98 were collapsed into M (missing); 96, 99 into Y (unscorable or invisible surface)

For purposes of scoring our outcome measures, calls distinguished by P as the first character are collapsed into the most similar caries status category (see Table 1, e.g., PD_2 _with D_2_), since transition to or from a surface with pits & fissure sealant (P) does not indicate a change in caries status. Calls that signify the need for surgical intervention are treated identically, so the D_2 _and D_3 _calls are collapsed into one category. For our primary outcome, calls that do not require surgical intervention (S, D_1_) are collapsed into one category. Finally, in contrast to ICDAS II, examiners make only one diagnostic judgment per tooth surface. Each central, lateral, and canine tooth is deemed to have five coronal (including the incisal) surfaces and four root surfaces.

**Table 1 T1:** Combined D_2_FS increment: Scoring weight of changes in tooth surface for primary outcome variable

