		**T**_**1**_**: Second call**							
**T_0_: First call**		**S [P D**_**1 **_**PD**_**1**_**]**	**D**_**2 **_**[D**_**3 **_**PD**_**2 **_**PD**_**3**_**]**	**F [FD**_**1**_**]**	**FD**_**2 **_**[FD**_**3**_**]**	**C [CD**_**1**_**]**	**CD**_**2 **_**[CD**_**3**_**]**	**Y**	**M**
	
	**S [P D_1 _PD_1_]**	0	1	1	1	0	0	0	0
	
	**D_2 _[D_3 _PD_2 _PD_3_]**	**-1**	0	0	0	0	0	0	0
	
	**F [FD_1_]**	**-1**	**0**	0	1	0	0	0	0
	
	**FD_2 _[FD_3_]**	**-1**	**-1**	0	0	0	0	0	0
	
	**C [CD_1_]**	**-1**	**0**	0	1	0	1	0	0
	
	**CD_2 _[CD_3_]**	**-1**	**-1**	**-1**	0	0	0	0	0
	
	**Y**	0	0	0	0	0	0	0	0
	
	**M**	0	0	0	0	0	0	0	0

S = sound

P = pit and fissure sealant

D_1 _= non-cavitated caries lesion

D_2 _= cavitated enamel caries lesion

D_3 _= caries lesion penetrating into dentin

F = filled

C = crowned

A primary examiner at each clinical center is scheduled to complete virtually all examinations. A back-up examiner can perform examinations in the event that the primary examiner is unavailable. A recorder is present for all caries examinations. Primary and back-up examiners and recorders from all three clinical centers participated in a four-day calibration session with a gold standard examiner and were certified by the DCC prior to the first baseline examinations. They also participate in refresher and reliability measurement sessions prior to the 12-, 24-, and 33-month examinations.

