The inclusion of non-cavitated lesions in the secondary analysis raises some interesting issues with regard to the relative weight given these lesions in the analysis compared to cavitated lesions. We have stated *a priori *our weighting scheme, but plan to analyze variations on this matrix to determine the sensitivity of the increment scores to several of our weighting decisions. Also, because both cavitated and non-cavitated lesions are recorded in this trial, the results should offer insight into the possibility of shortening caries trials by basing the principal analysis on non-cavitated lesion increments. Should a shorter trial be shown to be feasible in retrospect, this will have important implications for future caries trials. The typical three year duration and associated costs of such trials, has contributed to the reduction in such controlled studies in recent decades. Yet the need for this type of unbiased research result for caries preventive agents is undiminished, as discussed above.

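### The primary model adjusts for baseline caries with one undefined sum of decayed surfaces; separate non-cavitated and cavitated counts could gain some precision at almost no cost

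*Protocol article*

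**What the plan says.** Under Primary Outcome Analysis, the Protocol article puts treatment and center in the model, with "age and age-squared, intensity of preventive regimen, oral hygiene behavior measures" among the other adjustment terms. The model's only caries term is "severity of baseline caries, which is defined as the sum of decayed surfaces at the baseline examination". No separate D1 term appears, and the covariate definition does not say which codes count as decayed.

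The key to Table 1 reads "D_1 _= non-cavitated caries lesion", so D1 carries a D code and is called a caries lesion. For the primary outcome, however, Caries Examination says that "calls that do not require surgical intervention (S, D_1_) are collapsed into one category". The Discussion confirms that "both cavitated and non-cavitated lesions are recorded in this trial", and the Missing Data section expects baseline measures to be complete.

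Under Secondary Outcome Variable, a move from sound to D2 is weighted as two steps, with D1 as the intermediate one.

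**The concern.** A baseline covariate earns its place by explaining variation in the outcome between participants. Surfaces with D1 at baseline are, on the article's own account, one step from a scoring event. Surfaces that are already cavitated have passed that event. The phrase used for the covariate leaves two readings open:

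- **Cavitated only (D2/D3).** The model leaves out the recorded precursor of the outcome.
- **All lesions (D1 to D3).** The model gives one coefficient to surfaces that can score and to surfaces that cannot score from where they start.

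What is at stake is the standard error of the treatment effect. That matters somewhat here because the trial randomized 691 of a planned 750.

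**Working it through.** **1. What can score (Table 1, with the Primary Outcome Variable section).**

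| Baseline state | Transitions scoring +1 | Other cells |
|---|---|---|
| S, P, D1, PD1 (one row) | to D2, F or FD2 | 0 |
| F, FD1 (one row) | to FD2 | 0, or a bolded cell |
| C, CD1 (one row) | to FD2 or CD2 | 0, or a bolded cell |
| D2/D3, FD2/3, CD2/3 (three rows) | none | 0, or a bolded −1 |

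The primary analysis ignores the bolded cells. Every non-cavitated code can therefore score, and no cavitated code can score from its baseline state. A cavitated surface that is filled and later breaks down can still score on that later step.

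**2. The plan's own sample size.** Inputs from Sample Size: placebo increment μ = 3.7 (within 2.3 to 4.9), overdispersion φ = 3.0, rate ratio 0.80 ("assuming that the treatment might result in a 20% reduction"), "with power set at 80% and one-sided alpha at 0.025", and attrition of 10% per year. Allocation of 1:1 is assumed. The Poisson-regression formula for a binary covariate is

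N = φ(z₀.₉₇₅√V₀ + z₀.₈₀√V₁)² / (μ ln(RR)²), with V₀ = 4 and V₁ = 1/0.5 + 1/(0.5 × 0.8) = 4.5.

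This gives 530, and 530/0.70 = 757, close to the stated 750. With compounded attrition it is 530/0.729 = 727. The target therefore fits the central increment of 3.7.

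**3. What a variance cut would be worth.** Take 691 randomized and 27.1% compounded attrition, so 691 × 0.729 = 504 analysed, or 252 per arm. The Wald variance of the log rate ratio is 3.0 × (1/3.7 + 1/2.96)/252 = 0.00724, so SE = 0.0851. Power is Φ(0.2231/0.0851 − 1.96) = 74.6%. This formula is slightly more conservative than the one in step 2. It takes φ = 3.0 as what remains before a separate D1 term is added.

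| Assumed variance cut | Power |
|---|---|
| 0% | 74.6% |
| 5% | 76.7% |
| 10% | 78.9% |
| 20% | 83.4% |

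**4. How large the cut might be.** The planning cohorts did not measure D1, so its prognostic strength has to be assumed. The table shows illustrative negative binomial simulations at placebo mean 3.7. Each entry is the variance cut from using separate D1 and cavitated terms.

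| Assumptions | Against a cavitated-only sum | Against a pooled sum |
|---|---|---|
| 691 participants; 0–35% of events from D1 | 0–8% | 0–3% |
| 691; independent counts; 10–35% from D1 | 1–10% | 0–1% |
| 691; independent counts; D1 mean 6; marginal overdispersion held at 3.0; 5%, 20%, 35% from D1 | 0.2%, 4%, 13% | within ±1% (20–35% from D1) |
| 504; independent counts; cavitated log-coefficient 0.3; D1 log-coefficient 0, 0.15, 0.3, 0.5 | 0%, 2%, 7%, 19% | 4%, 2%, 1.5%, 3% |
| 691; D1 mean 6–10; 20–35% from D1; terms entered as ln(1 + count) | 12–20% | 2–5% |

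Worked example from the fourth row, at D1 coefficient 0.5. The mean SE is 0.0795 (cavitated only), 0.0728 (pooled) and 0.0717 (separate). The cuts are 1 − (0.0717/0.0795)² = 19% and 1 − (0.0717/0.0728)² = 3%.

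The last row is an upper scenario, for two reasons. Its gain includes the effect of the log form. Its cavitated-only SEs (0.0730 and 0.0761) also exceed the unadjusted value implied by the plan's own figures. With dispersion (3 − 1)/3.7 = 0.54 and 345.5 per arm, that value is √[(1/3.7 + 0.54 + 1/2.96 + 0.54)/345.5] = 0.070.

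**The case against.** The strongest reply is that this is a preference and not an error. The plan prespecifies adjustment for baseline severity, and using one count where two are possible neither biases the comparison nor invalidates the test. That is correct, and the point claims nothing more than precision.

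Second, the sum may already contain D1. The article labels D1 a "non-cavitated caries lesion" and uses a subscript where it means cavitated lesions only, whereas the covariate has none. This is plausible but not conclusive, because the primary outcome groups D1 with sound. If it is right, the gain shrinks to about 0–5%.

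Third, cavitated surfaces can predict new lesions elsewhere in the mouth, and the eligibility criteria use them that way. This stands, and it is a reason to keep the cavitated count as its own term.

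Fourth, age, oral hygiene and preventive regimen may already capture part of what D1 predicts. This also stands, and the documents cannot settle it.

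Fifth, a condensed article may leave covariate coding to a fuller document. The missing code list alone would therefore not be a finding. What remains is that the article commits to a single sum, and neither reading of that sum separates the two kinds of surface.

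A reader might go further and infer that precision already collected is being thrown away, worth some 95 to 170 participants (691/0.88 − 691 = 94; 691/0.80 − 691 = 173). The documents do not support this. It requires D1 to be excluded from the sum and a D1–outcome association that the documents never give.

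**Conclusion.** The point holds as a modest matter of efficiency. The single baseline severity covariate is undefined as to D1, and under either reading it fits the scoring of the primary outcome less closely than two counts would.

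The gain in variance of the log rate ratio is nil to roughly 10% if the sum excludes D1, rising to about 20% only under the strongest assumptions. It is about 0–5% if the sum includes D1. On the approximation above, a 5% cut is worth about 2 percentage points of power and a 10% cut about 4. All these figures rest on assumed D1 counts and associations and are illustrative. In the simulations, separate untransformed counts were essentially never worse than either reading of the plan.

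**What to change.** Before unblinding, replace the single severity covariate with two baseline counts:

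- non-cavitated surfaces: D1, PD1, FD1, CD1;
- cavitated surfaces: D2/D3, PD2/3, FD2/3, CD2/3.

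Fix the functional form at the same time. A log form, ln(1 + count), is optional: it performed no better than, or slightly worse than, raw counts where the two were compared directly. Listing the codes also settles what decayed means for this covariate, so no choice between two primary models is left open.

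The cost is one line in the model specification and one extra degree of freedom. The data are already collected.
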